**Fig. 1 Fig1:**
[figure not shown]
Study plan

Additionally, one first-degree relative of the index participant with CMM will be enrolled for the intergenerational preventive aspect of the proposal into the same arm of study A or B. The first-degree relative could be a male or female, ≥30 years of age, not necessarily staying in the same household, and could also be a child or sibling of the index participant (Figs. 2, 3, 4, 5, and 6).

**Fig. 2 Fig2:**
[figure not shown]
Health system challenges and gaps identified

**Fig. 3 Fig3:**
[figure not shown]
Plan-Do-Study-Act cycle

**Fig. 4 Fig4:**
[figure not shown]
Theory of Change. Study design: mixed-methods, type III effectiveness–implementation research

**Fig. 5 Fig5:**
[figure not shown]
Flow chart for implementing a lifestyle toolkit versus standard of care in individuals with cardiometabolic multimorbidity

**Fig. 6 Fig6:**
[figure not shown]
Participant flow diagram

### Criteria for discontinuing or modifying allocated interventions

Patient disinclination or dropout would be the criteria for discontinuing or modifying allocated interventions.

### Strategies to improve adherence to intervention/comparator protocols

For diet and nutrition, a Food Frequency Questionnaire would be administered at 0, 6, and 12 months. Additionally, participants would be requested to send a photograph of their food plate for calorie assessment (using the CalAI App) on three different occasions during the study period.

For physical activity, participants are encouraged to maintain log books of physical activity in minutes per day, and if available to use a step-counter to measure the number of steps per day.

For stress management, yoga sessions would be conducted online in the JAKs. A yoga trainer would schedule yoga sessions in one of the JAK centres with participants for that centre being guided in-person, while the other eight JAK centres join online for the session with participants encouraged to join from individual JAK centres. Nine such sessions of breathing exercises, postures, and mild stretching exercises are planned, one in each of the JAK centres, for the 9 weeks. The digital platform for the same has been created to facilitate the process.

For tobacco and alcohol cessation, counselling would be based on the WHO-ASSIST scores and planned accordingly with expert opinion sought in those needing the same.

For improving adherence to medications, a mix of digital prompts, tunes and jingles at weekly intervals for 4 weeks, and monthly for the next 9 months is planned as reminders to adherence and on the benefits of the same.

The intervention as envisaged is anchored in the public health system through the JAKs, with the interventions to be carried out by the JAK staff enabled and facilitated in all aspects by digital technology and a m-health platform.

In addition, each of the participants from the intervention arm has a password-encrypted access to the Shraddha app and portal which gives them access to health modules on lifestyle modifications. Participants are also given the liberty to upload health details like laboratory tests (sugar, glycated haemoglobin, etc.), or reach out with specific queries which would be addressed online in 24 h. The two-way app, to our mind, ensures ownership, participation, and would help curb dropouts.

Our previous experiences in the cohort using frontline health workers and digital platforms in the same cohort encourage us to utilise the same [34–36].

The endline survey would be done by ASHA workers, at the household, by the end of 12 months into enrolment into the study.

### Concomitant care that is permitted or prohibited during the trial

Standard concomitant care continues as directed by treating physician.

### Statistical analysis {20a}

Data will be anonymised and entered electronically on a secure storage system. Outcome data will be reported in accordance with Consolidated Standards of Reporting Trials (CONSORT) guidelines.

Multilevel modelling for repeated measurements will be used to compare the mean blood pressure (systolic and diastolic) and glycaemic levels over the study period in each site adjusted for individual covariates, where study participants are selected according to the intention-to-treat principle. Similarly, the quality of life will be assessed over and after the intervention.

A mixed-methods research approach will be used to assess the implementation according to eight domains according to the framework by Procter et al. for implementation research [37].

Quantitative measures of the implementation will be assessed by panel data regression to identify contextual factors that influence the implementation success, to identify changes throughout the study period, to identify variations and disparities in the implementation success across sites, and to evaluate the overall success of the implementation. Before the start of the study, the investigators will establish benchmarks and targets for each quantitative measure based on historical data, expert opinion, evidence-based guidelines, and stakeholders’ objectives. These targets will be used to facilitate monitoring of the implementation process and outcomes, allowing for timely adjustments and feedback.

Qualitative measures of the implementation will be assessed using constructivist grounded theory to understand how the intervention is perceived and experienced by the stakeholders and the intended beneficiaries. We will use purposive sampling to select initial participants for interviews and focus group discussions, and theoretical sampling to select additional participants and gather more data to develop and refine the emerging understanding through focused coding, memo writing, theoretical integration, reflexivity, and interpretation. We will validate the findings by engaging with participants to ensure that the theoretical framework accurately reflects their experiences and perspectives. In this way, we will identify key factors that contribute to or hinder the success of the toolkit’s implementation.

An economic evaluation of the intervention compared to SOC will consist of two analyses: (1) a cost-consequence analysis based on the observed results within the trial period and (2) a return on investment (ROI) analysis, expressing benefits in monetary terms relative to investments made, and expressing both the costs and the full range of benefits of an intervention in the same units (money), will also be conducted.

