## Abstract

**Abstract:** Lifestyle modification, including dietary interventions, physical activity, and stress management, has proven crucial in the non-pharmacological management of cardiometabolic diseases. However, the implementation of these interventions in the context of cardiometabolic multimorbidity (CMM) within the unique demographic and cultural milieu of India is inadequately explored, despite Indians exhibiting distinct susceptibility to cardiovascular diseases. This community-based study aims to address existing knowledge gaps by implementing a culturally tailored lifestyle toolkit based on the WHO-HEARTS framework among individuals with CMM and exploring the intergenerational preventive dimension. The study adopts a two-arm non-blinded cluster randomised controlled trial (c-RCT) design to include adults diagnosed with CMM, defined by the presence of two or more of diabetes mellitus, hypertension, stroke, or coronary heart disease, aged 18 years and above, providing informed consent, and agreeing to follow-up. The trial spans the ‘Epidemiology of Non-communicable Diseases In Rural Areas’ (ENDIRA) cohort in Ernakulam, Kerala. The intervention, ‘SHRADDHA lifestyle toolkit’, integrates guidance on diet, physical activity, stress management, tobacco and alcohol cessation, and drug adherence. It leverages frontline health workers and a digital health platform for implementation. Measurements involve use of point-of-care devices and digital tools. The study duration is 24 months, with a sample size of 2000 participants distributed across 18 clusters. Statistical analysis includes repeated-measures ANOVA and multilevel models, employing an intention-to-treat approach. The study’s novelty lies in its holistic approach, addressing various facets of CMM comprehensively.

**Trial registration: **The trial has been registered with the Clinical Trial Registry of India (CTRI) Reference Number—CTRI/2025/08/092529. Registered on August 6, 2025

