### Sample size {14}

The sample size was determined using computer-generated randomisation at the cluster level across 18 sub-centres (9 intervention and 9 control).

As this is a type III implementation study, the primary focus will be on evaluating implementation outcomes. In addition, effectiveness will also be assessed based on the following sample size estimation.

To detect a minimum clinically meaningful difference of 0.5% in HbA1c between the two groups, with 80% power, a two-sided alpha of 0.05, and assuming a standard deviation of 1.5% [33], the required sample size under individual randomisation was calculated to be 142 participants per arm.

Given the cluster design, with a planned cluster size of 90 participants and an intracluster correlation coefficient (ICC) assumed to be 0.05, the design effect was calculated as 5.45 using the formula DE = 1 + (m − 1) × ICC. After adjusting for clustering, the required sample size was 774 participants per arm.

The trial will include nine clusters per arm, with 90 participants per cluster (810 participants per arm), which exceeds the minimum required sample size. The fixed cluster size and number of clusters are determined by the structure of the ENDIRA cohort, within which this follow-up study is embedded.

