### Randomisation sequence generation {16a}

The study will employ simple randomisation at the cluster level and will randomise 18 sub-centres into intervention and control arms.

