### Definition of who will be included in each analysis (e.g. all randomised participants), and in which group

Each individual with cardiometabolic multimorbidity who meets the inclusion criteria will be analysed according to the allocation of their cluster on an intention-to-treat basis.

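### The abstract names repeated-measures ANOVA, which has no term for sub-centre clustering, and the methods word the effectiveness comparison by site instead of between arms

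*Protocol article*

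**What the plan says.** All references are to the protocol article.

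- **Abstract:** "Statistical analysis includes repeated-measures ANOVA and multilevel models, employing an intention-to-treat approach". It does not say which method serves which outcome.
- **Statistical analysis {20a}:** a multilevel model that allows for repeated visits is to compare blood pressure and glycaemia, and the comparison is worded as "glycaemic levels over the study period in each site adjusted for individual covariates". The sentence names no arm, and the section does not mention ANOVA. Methods for any additional analyses {20b} does not mention it either.
- **Sample size {14}:** the effectiveness target is "To detect a minimum clinically meaningful difference of 0.5% in HbA1c between the two groups", and the number per arm is multiplied by a design effect of 5.45 for clustering.
- **Randomisation sequence generation {16a}:** "simple randomisation at the cluster level and will randomise 18 sub-centres into intervention and control arms". Explanation for choice of comparator {6b} says that each sub-centre is a cluster and receives either the toolkit or standard of care.
- **Definition of who will be included in each analysis:** participants "will be analysed according to the allocation of their cluster on an intention-to-treat basis".

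**The concern.** There are two separate problems of wording.

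First, an ordinary repeated-measures ANOVA models the correlation between visits of the same person. It treats participants of the same sub-centre as independent. The article's own sample size rests on the opposite premise: it allows for an ICC of 0.05 and inflates the sample more than fivefold. An arm comparison without a cluster term would give a standard error that is far too small and a false-positive rate far above 5%.

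Second, the methods sentence describes how levels behave over time in each site. If site means sub-centre, each such comparison sits inside a single arm. A before-after change within an arm mixes any toolkit effect with secular trend and regression to the mean. Randomisation protects the comparison between arms, and the sentence does not state it.

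**Working it through.** **Reproducing the plan's sizing.** The inputs are all in Sample size {14}: difference 0.5, SD 1.5 (in HbA1c percentage points), two-sided alpha 0.05, power 0.80, m = 90 per cluster, ICC 0.05, nine clusters and 810 participants per arm.

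- Individual randomisation: n = 2 × [1.5 × (1.960 + 0.842) / 0.5]² = 141.3, rounded up to 142 per arm. This agrees with the article.
- Design effect: DE = 1 + (90 − 1) × 0.05 = 5.45. This agrees.
- Clustered requirement: 142 × 5.45 = 773.9, so 774 per arm. This agrees.

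**What happens if the arm test ignores clusters.**

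- Standard error ignoring clusters: 1.5 × √(2/810) = 0.075.
- Standard error under the plan's ICC: 1.5 × √(2 × 5.45/810) = 0.174, larger by a factor of √5.45 = 2.33.
- True size of the nominal 5% test: 2 × [1 − Φ(1.96/√DE)].

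| ICC acting on the tested contrast | DE at m = 90 | True type I error | Simulated |
|---|---|---|---|
| 0.05 (the plan's value) | 5.45 | 40.1% | 39.6% |
| 0.02 (assumption) | 2.78 | 24.0% | 23.5% |
| 0.01 (assumption) | 1.89 | 15.4% | 15.4% |

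The simulation used 18 clusters of 90, no arm effect and 4,000 runs per row.

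**What a cluster-respecting arm contrast gives.** With 810 per arm, 0.5/0.174 = 2.87. Power is 0.82 by the normal approximation and 0.77 by the noncentral t with 18 − 2 = 16 degrees of freedom. A valid analysis is therefore available with the planned clusters and data.

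**The contrast, passage against passage.**

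| Section | Comparison stated or implied |
|---|---|
| Sample size {14} | Between the two arms |
| Definition of who will be included in each analysis | By the arm of the participant's cluster |
| Statistical analysis {20a} | Levels over time, by site, with no arm named |

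The first two agree. The third is the sentence that an analyst would follow, and it does not state the contrast that the other two require.

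**The case against.** The best defence is that the article, read as a whole, points to a sound analysis. The methods name a multilevel model, which can carry a sub-centre effect. Participants are grouped by their cluster's allocation, and the sample size is for a difference between arms with a design effect. The word site is not defined in the analysis section and may simply mean the cluster level of the model. ANOVA appears only in the abstract, next to multilevel models. All of this stands. A reader might infer that the plan can give no valid between-arm estimate, but the documents do not support that.

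The 40% figure can also be questioned. It applies the plan's ICC to the tested contrast. In a test of arm-by-time, stable differences between sub-centres cancel, and the article gives no ICC for change. The number with HbA1c may also be smaller, because the consent provisions {26b} describe HbA1c sampling among cardiac patients with type 2 diabetes. Assume that the 37.3% diabetic share given in Trial setting {9} for people with cardiovascular disease applies. Then m is about 0.373 × 90 = 34, DE = 1 + 33 × 0.05 = 2.65, and the error is about 23%. So the error should be given as a range, with 40% for the plan's stated ICC and cluster size.

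Other stronger readings also fail:

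- **Participants with a missed visit are dropped, against intention to treat.** Ordinary ANOVA does this by default, but the missing-data section {20c} provides for imputation.
- **BMI and medication adherence have no model.** Both are in the objectives, but a full analysis plan may cover them.
- **The tests are too liberal for 18 clusters.** The article nowhere specifies normal-based tests.

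None of this removes the ANOVA from the abstract or puts an arm comparison into the methods sentence.

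**Conclusion.** The point holds as two errors of wording. The abstract names a method that ordinarily ignores the clustering built into the trial's own design effect and that the methods sections do not contain. The methods sentence does not state the between-arm contrast that the sample size and the intention-to-treat definition require.

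If the ANOVA were used for the arm comparison, a nominal 5% test would have a true type I error of about 40%. This assumes 90 participants per sub-centre and that the plan's ICC of 0.05 acts on the tested contrast. At an assumed ICC of 0.01 to 0.02 the error is 15% to 24%, still at least three times nominal. With equal cluster sizes the damage is to the standard error, interval and p-value; the point estimate is not biased.

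The weight is limited by the trial's priorities. Sample size {14} and Outcomes {12} make implementation outcomes primary, so this concerns the effectiveness objective.

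**What to change.** 1. Delete repeated-measures ANOVA from the abstract.
2. Restate the effectiveness sentence in Statistical analysis {20a} as the between-arm difference at 12 months from one linear mixed model of the 6- and 12-month values. Fixed effects are arm, visit, arm-by-visit and the baseline value of the outcome. Random effects are sub-centre and participant.
3. Name a small-sample degrees-of-freedom correction suited to 18 clusters, such as Kenward-Roger or Satterthwaite.

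The cost is a change of wording. The visits and measurements are already in Participant timeline {13}. The downside is slightly wider intervals: with 16 degrees of freedom the critical value is 2.120 instead of 1.960, and 2.120/1.960 = 1.08, so about 8% wider. Before baseline adjustment, and at the plan's ICC, the half-width for HbA1c goes from 1.960 × 0.174 = 0.34 to 2.120 × 0.174 = 0.37 percentage points.

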### Definition of who will be included in each analysis (e.g. all randomised participants), and in which group

Each individual with cardiometabolic multimorbidity who meets the inclusion criteria will be analysed according to the allocation of their cluster on an intention-to-treat basis.

### Methods for any additional analyses {20b}

Multilevel modelling and panel data regression to explore contextual factors; qualitative constructivist grounded theory for implementation data; economic evaluations: cost-consequence analysis and ROI analysis.

### How missing data will be handled in the analysis {20c}

Nonadherence will be managed by the intention-to-treat analysis and if there are too many missing data, imputations will be considered. Mixed method analysis will be considered for intention-to-treat analysis. Also depending on the percentage of data missingness and assumption for data missing in the study variables, appropriate missing data imputation technique will be used.

#### Study duration and follow-up

The study will be of 24 months including 12 months of intervention, and outcomes will be measured at baseline 6 and 12 months for primary and secondary outcomes.

### Harms: definition and assessment {22}

As this study is implementation of a lifestyle toolkit, no adverse events or serious adverse events and harms from the intervention are anticipated. But if there are any, they will be reported to relevant regulatory bodies such as Project Management Group, Trial Steering Committee, District Health Authority, and Ethics Committee. Trial deviations will be reported to the ethical committee.

### Ethical consideration {24}

Ethics approval for the project was granted by the IEC of AIMS-Kochi, dated ECASM-AIMS-2024-001. The clinical trial has been registered with the CTRI (Clinical Trial Registry of India) with a trial registration number of CTRI/2025/08/092529. Confidentiality of the participants will be ensured during recruitment of the participants, data collection, transcription, data analysis, and dissemination of research results. It will be done by assigning the numbers to the participants while recruiting and coding them during analysis. The data will be stored for 5 years. The results generated from this research will be freely shared with the public and research community through research publications.

### Plans for communicating important protocol modifications to relevant parties {25}

In case of protocol modifications, steps will be taken to obtain IEC approval for amendments, update CTRI, inform sponsor/funder, investigators, trial staff, and where relevant participants.

### Who will obtain informed consent or assent from potential trial participants or authorised proxies, and how {26a}

Informed consent will be taken by the accredited social health activist (ASHA) of the area who will be collecting the data. The data collection will be through an application called SHRADDHA installed in tablet PCs provided to them. The participant’s digital signature will be obtained on the tablet.

### Additional consent provisions for collection and use of participant data and biological specimens in ancillary studies, if applicable {26b}

Blood samples will be collected to assess random blood sugar and HbA1c among cardiac patients with type 2 DM after obtaining consent. These samples will be tested using point-of-care devices and will not be stored. We will request consent for review of participants’ medical records and for the collection of blood samples to assess random blood sugar and HbA1c among the cardiac patients with type 2 diabetes. But this trial does not involve collecting biological specimens for storage.

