### Trial setting {9}

The study is to be carried out in the ENDIRA cohort of Ernakulam, Kerala [22, 23]. The ENDIRA (‘Epidemiology of Non-communicable Diseases In Rural Areas’) cohort (*n* = 114,064) includes all individuals from five panchayats (villages) in Ernakulam district, Kerala. Four of the five panchayats have family health centres (FHCs), and one community health centre (CHC), which are further divided into 18 sub-centres and 75 wards having 2064 individuals with documented cardiovascular diseases. Among these individuals, 37.3% were diabetic, 53.5% hypertensive, 30.5% were dyslipidaemic, 16.8% were tobacco users, and 23.2% were alcohol users [24]. Leveraging previous research initiatives in this region ensures the seamless integration of the current study and enhances its generalisability to a broader context.

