### Eligibility criteria for participants {10}

Inclusion criteria: individuals diagnosed with CMM (defined as the presence of two or more of the following conditions: diabetes mellitus, hypertension, stroke, or coronary heart disease); stroke would include a documented ischaemic or haemorrhagic cerebrovascular accident as diagnosed from symptoms or imaging studies; coronary heart disease as defined by individuals with a history of an acute coronary syndrome, or diagnosed coronary artery disease defined as 50% stenosis of one or more of the epicardial coronaries on CT or conventional coronary angiography; or wall motion abnormalities (WMA) on echocardiography or nuclear imaging suggestive of an old myocardial infarction; age ≥ 18 years, providing informed consent for participation and agreeing to follow-up.

Exclusion criteria: individuals with cognitive impairment who are unable to carry out instructions; bedridden individuals; individuals with other significant confounding health conditions additionally like malignancy or chronic airway disease; individuals ≥75 years of age; individuals with a terminal medical condition; pregnant or lactating mothers.

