### Participant timeline {13}

**Table Tabb:** 

Timepoint	Trial period				
	Enrolment		Post-randomisation		Close-out
	(−ti to 0)	0	t1 (6 mo)	t2 (12 mo)	tx
Enrolment					
Eligibility screen	X				
Informed consent	X				
Baseline demographics	X				
Cluster randomisation (sub-centres: arm A/arm B)		X			
Intervention/comparator					
Shraddha lifestyle toolkit (arm A)		X			X
Standard of care (arm B)		X	X	X	X
Assessments					
Clinical measures (BP, weight, BMI)	X		X	X	X
Laboratory (HbA1c)	X		X	X	X
Diet (FFQ/calorie tracking)	X		X	X	X
Physical activity (GPAQ)	X		X	X	X
Substance use (WHO-ASSIST)	X		X	X	X
Medication adherence (MMAS-8)	X		X	X	X
Mental stress (PSS-10)	X		X	X	X
Quality of life (EQ-5D-L3)	X		X	X	X
Implementation outcomes (acceptability, adoption, appropriateness, fidelity, cost effectiveness)			X	X	X

Baseline = 0; t1 = 6 months (midline); t2 = 12 months (endline). The arrow indicates continuous delivery of the Shraddha lifestyle toolkit (mHealth messages, JAK visits, yoga sessions) from allocation to endline. Protocol v4 (26 September 2025); IEC ASM-AIMS ECASM-AIMS-2024-001; CTRI/2025/08/092529

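### The HbA1c sample size counts all 90 participants per cluster, but the consent section describes HbA1c sampling in cardiac patients with type 2 diabetes; if that governs, power falls below the stated 80%

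*Protocol article*

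**What the plan says.** **Sample size {14}.** The effectiveness calculation is for HbA1c: "To detect a minimum clinically meaningful difference of 0.5% in HbA1c between the two groups", "with 80% power, a two-sided alpha of 0.05", "assuming a standard deviation of 1.5" percentage points. This gives 142 per arm under individual randomisation. It is then inflated "with a planned cluster size of 90 participants and an intracluster correlation coefficient (ICC) assumed to be 0.05", for a design effect of 5.45 and 774 per arm. Nine clusters of 90 give 810 per arm, which the section says is more than enough. Every enrolled participant is therefore counted as supplying an HbA1c value.

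**Consent provisions {26b}.** "Blood samples will be collected to assess random blood sugar and HbA1c among cardiac patients with type 2 DM". The same section repeats the group when it describes the consent to be requested for blood sampling. No other section on sampling names who is tested.

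**Eligibility {10}.** Participants need "two or more of the following conditions: diabetes mellitus, hypertension, stroke, or coronary heart disease". Hypertension with stroke qualifies without diabetes. Diabetes with hypertension qualifies without cardiac disease.

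**Objectives {7}, Participant timeline {13}, Measurements.** The fourth objective concerns glycaemic control in individuals with cardiometabolic multimorbidity generally. The timeline and the measurements section list HbA1c at baseline, 6 and 12 months and limit it to no subgroup.

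**Trial setting {9}.** The cohort has 2064 people with documented cardiovascular disease across 18 sub-centres. "Among these individuals, 37.3% were diabetic, 53.5% hypertensive".

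**The concern.** The number in the power statement and the number described for blood sampling belong to different groups. HbA1c is the only outcome with a sample size, it appears in the fourth objective, and Table 2 defines cost-effectiveness as the incremental cost of a 0.5% improvement in it. If field staff follow the consent item, many enrolled participants will have no HbA1c value, and the comparison of 810 with 774 no longer describes the data. Baseline values that are not taken at enrolment cannot be recovered later. If staff follow the schedule, consent for blood sampling has been described for a narrower group than the one tested.

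**Working it through.** **Inputs.** From Sample size {14}: difference 0.5, SD 1.5, two-sided alpha 0.05, power 80%, 9 clusters per arm, 90 per cluster, ICC 0.05. From Trial setting {9}: 2064 people with documented cardiovascular disease, 37.3% diabetic, 18 sub-centres.

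**Step 1: reproduce the plan.**
- n = 2 × (1.96 + 0.8416)² × (1.5/0.5)² = 141.3, rounded up to 142.
- DE = 1 + 89 × 0.05 = 5.45, and 142 × 5.45 = 773.9, rounded up to 774.

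All three figures agree with the protocol. The arithmetic is sound; the question is how many participants it applies to.

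**Step 2: power for m tested per cluster.**
- DE(m) = 1 + (m − 1) × 0.05
- effective n per arm = 9m / DE(m)
- SE = 1.5 × √(2 / effective n)
- power (normal) = Φ(0.5/SE − 1.96)

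As a sensitivity check, the same 0.5/SE is used as the noncentrality of a t test on 18 − 2 = 16 degrees of freedom.

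**Step 3: number needed.** At m = 70, DE = 4.45, effective n = 630/4.45 = 141.6 and power is 80.1%. At m = 69 it is just under 80%. The plan's method therefore needs about 70 tested per cluster, or 78% of 90.

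**Step 4: ceiling from the cohort figures.** 2064 × 0.373 = 770 people, and 770/18 = 42.8 per cluster, or 385 per arm. DE = 1 + 41.8 × 0.05 = 3.09, effective n = 385/3.09 = 124.6 and SE = 0.190. Power is 74.9%. At that cluster size the requirement would be 142 × 3.09 = 439 per arm. The ceiling counts every diabetic on the list, spread evenly, before the age limit, other exclusions, refusal and dropout.

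**Step 5: range.** The tested share of enrollees is not stated, so the rows for 70%, 50% and 37.3% are assumptions.

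| Tested per cluster | DE | Effective n per arm | Power, normal | Power, 16 df |
|---|---|---|---|---|
| 90 (all) | 5.45 | 148.6 | 82.0% | 77.0% |
| 63 (70% of 90) | 4.10 | 138.3 | 79.2% | 74.0% |
| 45 (50% of 90) | 3.20 | 126.6 | 75.5% | 70.2% |
| 42.8 (cohort ceiling) | 3.09 | 124.6 | 74.9% | 69.5% |
| 33.6 (37.3% of 90) | 2.63 | 114.9 | 71.5% | 66.0% |

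The 70% row would need 63 × 18 = 1134 diabetic cardiac patients, more than the 770 on the cohort's figures. It shows that even a generous share stays just under 80%.

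**Step 6: dependence on the ICC.** At ICC 0.03 and 33.6 tested per cluster, power is 83.0% (normal) or 78.1% (16 df).

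**Step 7: effect of baseline adjustment.** Assume a correlation r between baseline and follow-up HbA1c that scales the whole variance by 1 − r². At 33.6 per cluster, ICC 0.05 and 16 df, r = 0.5 gives 78.2% and r = 0.6 gives 84.2%.

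**The case against.** The strongest reply is that the consent item does not say HbA1c is measured in no one else, and that it answers a reporting item on ancillary use of specimens. The sections that govern conduct (objective, schedule, measurements) have no restriction. If they prevail, 810 does exceed 774 and the plan's method gives 82%. This stands: the shortfall is conditional on which section is followed. It does not remove the conflict, because the only section that names the tested group names a narrower one, twice.

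Four further points limit the size of the claim.
- The 37.3% is the diabetic share of people with documented cardiovascular disease, not of enrolled multimorbid participants, among whom diabetes may well be commoner. The 71.5% figure is thus one scenario. The ceiling of 770 does not depend on that share, because it already counts every diabetic on the list.
- The 16-df figures include a loss that has nothing to do with who is tested: full testing gives only 77.0% on that basis. Like for like, the loss at the ceiling is 82.0% to 74.9%, or 77.0% to 69.5%.
- At a smaller ICC the shortfall shrinks or vanishes, although 0.05 is the plan's own value.
- The statistical analysis section already foresees multilevel repeated-measures models with individual covariates, which could recover power.

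A reader might infer that the sample size is wrong on either reading, because non-diabetic participants would dilute the effect under universal testing. The document does not support this. It states 0.5% as the difference between the two groups and does not tie it to diabetics, and a dilution figure requires the further assumption that non-diabetics do not respond at all. What can be asked is that the sponsor confirm which population the 0.5% and the SD of 1.5% describe.

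**Conclusion.** The protocol contradicts itself on who has HbA1c measured, and its power statement holds on one reading only. With everyone tested, the plan's method gives 82.0%. With testing as the consent item describes, the cohort's own counts give at most about 75%, and 71.5% if 37.3% of each 90 are tested. The loss is moderate because the design effect falls as fewer people per cluster are tested. These figures rest on ICC 0.05, SD 1.5, equal cluster sizes, the recorded cohort counts still holding, and cardiac patients being read as those with documented cardiovascular disease. It would go too far to conclude that HbA1c will certainly be restricted or that 80% power is certainly lost. Since the declared primary outcomes are implementation outcomes, this is a point that should be fixed, not one that puts the primary aim in doubt.

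**What to change.** Make Sample size {14}, Participant timeline {13}, Measurements and the consent provisions {26b} name the same HbA1c population. Two resolutions are open:

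1. Test all participants, in line with the fourth objective. Correct the consent item, and confirm that a difference of 0.5% with SD 1.5% refers to the mixed population of diabetic and non-diabetic participants.
2. Keep a restricted group. State it in every section, and replace the 90, 5.45, 774 and 810 by the expected number tested per cluster with the matching design effect and power, shown over a range of tested shares and ICCs.

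In either case, compute power with 16 degrees of freedom and name baseline HbA1c, which is already collected, as a covariate in the HbA1c model. At about 34 tested per cluster and an assumed correlation of 0.5 to 0.6, that brings 16-df power to about 78–84%.

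The cost is wording in four sections, a recalculation, and a somewhat less favourable unadjusted power figure. The first option may add point-of-care tests, which the schedule already lists. The change is best made before baseline sampling is complete.
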